## 2. Stepped-care for anxiety/depression

Dizzy older patients with the risk factor 'anxiety and/or depression' (defined as the presence of Generalised Anxiety Disorder (GAD), Panic Disorder (PD), or Major Depressive Disorder (MDD)), will follow a stepped-care program, according to the Trimbos Multidisciplinary Guideline Anxiety Disorders and the Trimbos Multidisciplinary Guideline Depression. The presence of GAD/PD/MDD will be assessed by the and GAD-7, Patient Health Questionnaire, panic module (PHQ-PD), and the PHQ-9 (see next paragraph). Stepped-care has been proven to be effective in older people with anxiety and/or depression.

Stepped-care involves four subsequent treatment steps for anxiety and depression in primary care. A practice nurse mental health (POH-GGZ) of the patient's own general practice guides the patient through the various steps of the program. All participating POH's-GGZ will receive a training of two days about stepped-care, guided self-help and problem solving therapy before start of the intervention. The GP is easily accessible for the POH-GGZ to discuss about a patient if needed. The steps of the program involve: (1) watchful waiting, 6 weeks; (2) bibliotherapy, 6 weeks; (3) Problem Solving Therapy, 6 weeks; and (4) indicated treatment. The patient will proceed to the next step after every 6 weeks in case of persisting complaints. The POH-GGZ will seek for an alternative treatment step if a patient is not motivated for an offered intervention. The intervention, as part of our study, is finished when the patient does not suffer from anxiety/depression anymore, or when the patient still suffers from anxiety/depression and proceeds to step 4.

*Step 1. Watchful waiting.* The first 6 weeks consists of a period of watchful waiting, because it is known that depressive/anxiety symptoms often disappear spontaneously over time. In this 6 week period, the patient will be invited by the POH-GGZ for a first consultation to get familiar with the POH-GGZ. During this introductory consultation the POH-GGZ will shortly inform the patient about depression/anxiety and the stepped-care program. After 6 weeks the POH-GGZ will invite the patient again. The patient will be asked to fill out the GAD-7, PHQ-PD and PHQ-9. In case of persisting anxiety and/or depression the patient will go to step 2.

*Step 2. Bibliotherapy.* During this step the patient will start with a guided self-help course (based on Lewinsohn's 'Coping with Depression' course). This self-help course is based on cognitive behavioural techniques and takes 6 weeks. The patient will receive a course book and every week, the patient will read about new insights and skills to cope with anxiety and/or depression. The book consists of information and exercises, which the patient can work through at his/her own pace. The POH-GGZ will support the patient by contacting the patient by telephone every two weeks, and by providing extra guidance if necessary. Since many patients of our population will be visual impaired, the POH-GGZ will also receive a digital version of the course to be able to print the text in a large size if necessary. After 6 weeks the POH-GGZ will invite the patient. The POH-GGZ will discuss the current depressive/anxiety symptoms and the patient will be asked to fill out the GAD-7, PHQ-PD and PHQ-9 again. In case of persisting anxiety and/or depression the patient will go to step 3.

*Step 3. Problem Solving Treatment (PST).* PST is a brief cognitive behavioural intervention that focuses on practical skill building, education and managing depressive symptoms. The goal is to achieve a reduction in mental health problems by stimulating an active attitude towards everyday problems. PST will be offered by the POH-GGZ and takes a maximum of 7 sessions at the general practice.

At the end of the PST-course the POH-GGZ will discuss the current depressive/anxiety symptoms and will ask the patient to fill out the GAD-7, PHQ-PD and PHQ-9 again. If a depression and/or anxiety still exists the patient is offered to go to step 4.

*Step 4. Indicated treatment.* The POH-GGZ will discuss the outcomes of the previous treatment steps with the GP if the patient is still suffering from anxiety and/or depression after the preceding steps. The GP will then have a consultation with the patient to assess what would be an appropriate next therapy for the patient (e.g. starting with antidepressants). The GP will then initiate the treatment.

### 3. Exercise therapy for risk factor impaired functional mobility

Dizzy elderly with the risk factor 'impaired functional mobility' (defined as a TUG score of 20 seconds or more), will receive standardized exercise therapy by a physiotherapist. Earlier research has shown that exercise therapy aiming to improve strength and balance in older people has a positive effect on mobility and reduces rate of falls and risk of falling. The exercise therapy implies training in a group session of one hour twice a week for eight weeks and will focus on strength (including resistance) and balance.

The program starts with 15 minutes warming up exercises in standing and walking with different combinations of head, trunk, arm and leg movements. This will be followed by a circuit training with 8 stations. The patients will perform a two minute exercise at every

station and will perform two laps of the circuit. The stations include the following exercises: standing on foam with eyes closed, standing on foam while flexing the knees and turning the head from side to side, a walking exercise with slalom between cones, knee flexor/extensor training with an ankle cuff, hip abductor/adductor training with an ankle cuff, standing up on toes, and standing on heels. All exercise of the circuit will be individually tailored by performing the exercises with or without extra support to remain standing, varying with the weight of the ankle cuff, standing or walking on heels and toes and standing or jumping on the trampoline. The exercise therapy will end with a cooling down of 10 minutes. The program will be accompanied by music of the group's preference.

No adverse reactions other than musculoskeletal discomfort related to exercise therapy has been described, in particular no fall related injuries occurring during exercise programs have been described.

#### Usual care

All included patients of group A and B (n=125) will receive usual care by their GPs. Participating GPs will receive a written instruction, asking them to diagnose causes of dizziness according to the Dutch guideline on dizziness and to treat identified disorders according to the guidelines of the Dutch College of GPs.

### **5.2 Use of co-intervention (if applicable)**

Not applicable.

### **5.3 Escape medication (if applicable)**

Not applicable.

**6. INVESTIGATIONAL PRODUCT**

Not applicable.

**7. NON-INVESTIGATIONAL PRODUCT**

Not applicable.

## 8. METHODS

### 8.1 Study parameters/endpoints

#### 8.1.1 Main study parameter/endpoint

The primary clinical outcome is dizziness related impairment, which will be assessed using the DHI. For the validation study we will dichotomize all DHI scores. In the intervention study we will use the difference in the 1-year DHI score change between patients in the intervention group and patients in the control group.

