### 4.4 Sample size calculation

#### Intervention study

The sample size calculation for our intervention study is based on the difference in 1-year DHI score change between the high-risk intervention group and the high-risk usual care group. We consider a DHI score difference of 12 or more to be a clinically relevant difference. The mean DHI score of patients above 65 consulting their GP because of dizziness is 36.3 with a standard deviation of 19.9. In order to detect a clinically relevant

difference with  $\alpha=0.01$  and  $\beta=0.90$  we used the following formula to calculate the sample size:

$$n = 2(2.58+1.28)^2 \cdot S^2/D^2$$

With  $n$  = number of patients,  $S$  = standard deviation,  $D$  = clinically relevant difference

A group size of  $n=82$  is sufficient  $(2(2.58+1.64)^2 \times 19.92^2/12^2)^{29}$ . However, we need to apply an extra correction since the proposed study is a cluster randomised trial. The correction that needs to be applied by performing an cluster randomised trial can be calculated with the following formula:

$$n = 1+(k-1) \cdot \rho$$

With  $n$  = number of patients,  $k$  = cluster size,  $\rho$  = intra-class correlation (ICC)

Based on secondary analysis of DIEP data we expect a cluster size of 5 patients per practice. An ICC of 0.01 is often used in sample size calculation in primary care research. However, we used an ICC of 0.05 to get a more conservative sample size. The correction factor for performing a cluster randomised trial is 1.2  $(1+(5-1) \cdot 0.05)$ . This means that a groups size of  $n = 99$   $(1.2 \cdot 82)$  is sufficient. Taking into account a loss to follow-up of 20% we need 124 participants in each arm. Thus, a total of 250 patients will be included in the intervention study.

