### 8.2 Randomisation, blinding and treatment allocation

Randomisation will take place at practice level. Randomisation will be executed by a researcher who is not involved in the selection of the practices (concealment of allocation). Practices will be randomly assigned to intervention practice or control practice. Stratification will take place for practice type (solo or group practice) and area (practice in disadvantaged areas or not) and block randomization will be used to create similar distributions in the different study arms. Randomisation of practices will be executed before inclusion of patients.

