#### II. Intervention study

We will perform both intention-to-treat and per-protocol analysis. We will use univariate and multivariate analyses to compare outcomes of usual care and intervention group. To investigate the effectiveness of the risk factor-guided intervention, we will use a repeated-measures mixed-effect (RMME) model to assess differences in the 1-year DHI score change, adjusted for potential confounders.

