### 11.2 Recruitment and consent

#### Practices

This study will be embedded in the Academic Network of General Practices of the VU Medical Center (ANH-VUmc, [www.anh-vumc.nl](http://www.anh-vumc.nl)) and the General Practitioners Cooperative Twente (Twentse huisartsenonderneming Oost Nederland, [www.thoon.org](http://www.thoon.org)). After randomisation, all GP's in the participating practices will be informed about the outcome (intervention practice or control practice) of the randomisation. At this point the GP's will also receive extra information about the study and instructions for the GPs, specified to the situation of the practice (intervention or control practice). The following care professionals will be invited for trainings: pharmacists who will participate in group meetings for FRID-analysis; physiotherapists for the physiotherapy intervention; and POH-GGZs and psychologists who will participate in the stepped-care program.

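### The primary analysis compares 1-year DHI change without committing to adjustment for baseline DHI or the two randomisation strata; a baseline- and strata-adjusted 12-month contrast would be better and costs nothing

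*Protocol*

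**What the plan says.** Section 8.1.1 sets the primary comparison of the intervention study: "we will use the difference in the 1-year DHI score change between patients in the intervention group" and those in the control group. Section 4.4 sizes the trial on the same quantity; its calculation is "based on the difference in 1-year DHI score change between the high-risk intervention group and the high-risk usual care group".

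Section 10.1 (II. Intervention study) names a mixed-effect model for repeated measures "to assess differences in the 1-year DHI score change, adjusted for potential confounders". It names no covariate. It also states: "We will use univariate and multivariate analyses to compare outcomes of usual care and intervention group".

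Section 8.2 describes the randomisation of practices: "Stratification will take place for practice type (solo or group practice) and area (practice in disadvantaged areas or not"). Neither factor is mentioned anywhere in section 10. DHI is collected at baseline, 3, 6 and 12 months in groups B and C (section 8.3 and its measurement table). The protocol does not say whether the baseline value enters the model as a covariate, as one of the repeated outcomes, or only as the subtracted term in the change.

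Two statements bear on imbalance. Section 8.2: "Randomisation of practices will be executed before inclusion of patients". Section 11.2: "After randomisation, all GP's in the participating practices will be informed about the outcome". Under section 11.2 the same GPs then identify patients in consultations and exclude patients from the search lists.

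**The concern.** A comparison of change with no baseline term assumes that a patient who starts one point higher is expected to finish one point higher, that is, a baseline slope of 1. Entry requires DHI of at least 30 (section 4.2), so some regression to the mean is expected and a slope below 1 is plausible. Two things follow when the slope is not 1:

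- The comparison has more variance than one that estimates the slope.
- The part (1 − slope) of any baseline difference between arms appears as treatment effect.

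The second matters more here than in an individually randomised trial. Patients enter after allocation, through GPs who know it, so a baseline difference can arise from recruitment as well as by chance.

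The strata are a smaller matter. They were built into the allocation, so the primary model should normally reflect them, and they are known before any outcome is seen.

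**Working it through.** **The plan's own figure.** Inputs from section 4.4: D = 12, SD = 19.9, z-values 2.58 and 1.28, cluster size 5, ICC 0.05, 20% loss.

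- Per arm: 2 × (2.58 + 1.28)² × 19.9² / 12² = 81.9, so 82.
- Design effect: 1 + 4 × 0.05 = 1.2. Then 82 × 1.2 = 98.4, so 99.
- Loss: 99 / 0.8 = 123.75, so 124 per arm.

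This reproduces the stated 82, 99 and 124. The 19.9 is the SD of a single score. With equal SDs the change SD is 19.9 × √(2(1 − r)), which equals 19.9 only at r = 0.5.

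**Precision, SD 19.9 at both times.** r is the baseline-to-12-month correlation. It is not in the protocol; 0.3 to 0.7 is an assumption.

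- Var(change) = 2(1 − r) × 396
- Var(baseline-adjusted) = (1 − r²) × 396
- Ratio, adjusted to change = (1 + r)/2

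| r | change | adjusted | reduction |
|---|---|---|---|
| 0.3 | 554 | 360 | 35% |
| 0.5 | 396 | 297 | 25% |
| 0.7 | 238 | 202 | 15% |

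Under these assumptions, with 99 analysed per arm (effective size 99/1.2) and α = 0.01, power for unadjusted change against baseline-adjusted is 76% against 93% at r = 0.3, 90% against 97% at r = 0.5, and above 99% for both at r = 0.7.

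A simulation with 20 practices of 5 patients per arm, ICC 0.05 and no entry restriction agrees. The variance ratio (change to adjusted) was 1.40 at r = 0.4 and 1.23 at r = 0.6; theory gives 1.43 and 1.25. Per point of baseline imbalance the change estimate moved by −0.60 and −0.39, and the adjusted estimate by 0.01 or less.

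**Precision with entry at DHI ≥ 30.** Take the section 4.4 distribution (mean 36.3, SD 19.9) as normal and truncate it at 30 (assumption).

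- a = (30 − 36.3)/19.9 = −0.317; λ = φ(a)/(1 − Φ(a)) = 0.608
- Mean = 36.3 + 19.9 × 0.608 = 48.4
- Variance = 396 × (1 + aλ − λ²) = 173.5, so SD ≈ 13.2

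Reading A: r is the correlation before selection. The slope is r, and Var(change) = (1 − r²) × 396 + (1 − r)² × 173.5.

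Reading B: r is the correlation among those selected, with follow-up SD 19.9. The slope is r × 19.9/13.17, and Var(change) = 173.5 + 396 − 2r × 19.9 × 13.17.

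| r | adjusted | A: slope, change, reduction | B: slope, change, reduction |
|---|---|---|---|
| 0.3 | 360 | 0.30, 445, 19% | 0.45, 412, 13% |
| 0.5 | 297 | 0.50, 340, 13% | 0.76, 307, 3% |
| 0.7 | 202 | 0.70, 218, 7% | 1.06, 203, 0% |

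**Imbalance.** If the intervention arm starts d points higher, the unadjusted change difference shifts by −(1 − slope) × d. For an illustrative d = 5:

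- slope 0.3: −3.5 points
- slope 0.5: −2.5 points (2.5/12 = 21% of the target difference)
- slope 0.7: −1.5 points
- slope 0.76 (reading B, r = 0.5): about −1.2 points

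For scale, by chance alone the SE of the baseline difference is about 13.2 × √(2 × 1.2/125) = 1.8. Five points is therefore about 2.7 SE and would need recruitment differences to arise.

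**Strata.** The protocol gives no figure for how strongly practice type or area relates to DHI, so the gain from including them cannot be computed.

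**The case against.** The strongest reply is that nothing is excluded. The phrase "adjusted for potential confounders" could cover baseline DHI and both strata, and a covariate list is often left to an analysis plan, which may exist. Change analysed with baseline as a covariate gives the same treatment effect as the 12-month score analysed with that covariate. A mixed model with baseline as a repeated outcome and a common baseline mean would also deal with imbalance. This stands: the loss and bias above arise only if baseline is not adjusted for. A reader might infer that the protocol rejects baseline or strata adjustment; the text does not support that.

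A reader might also infer that covariates are to be picked by testing them against the outcome. The text does not say so. The sentence "We will use univariate and multivariate analyses to compare outcomes of usual care and intervention group" is about comparing the arms and most naturally means unadjusted and adjusted comparisons. No selection procedure is described.

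On size, the 25% reduction at r = 0.5 ignores the entry threshold, and the restricted figures are the relevant ones. Under reading B the slope passes 1 at r ≈ 0.66 (13.17/19.9), so a slope below 1 is plausible but not certain. The 5-point imbalance is an illustration, not an estimate.

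Finally, recruitment after allocation can unbalance factors other than DHI, so adjusting for further patient-level factors in the primary model is defensible if they are prespecified.

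What remains is that sections 8.1.1 and 4.4 do fix a change comparison, and section 10 commits neither to baseline DHI nor to the strata. A better-defined contrast is available at no cost, so the point is more than a missing list.

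**Conclusion.** The point holds as a free improvement to the primary analysis, not as a demonstrated error in it. As written, the protocol allows a change comparison with the baseline slope held at 1 and the strata left out.

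If it were run that way, baseline adjustment would reduce variance by about 0% to 19% under the entry restriction (35% to 15% without it), for an assumed r of 0.3 to 0.7. The gain is never negative. Each point of baseline imbalance would shift the effect by (1 − slope), for example 0.5 points at slope 0.5.

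These figures rest on a correlation that the protocol does not give, on a truncated normal baseline, and on a follow-up SD derived from or set at 19.9. The direction does not depend on them: estimating the slope is never less precise than fixing it at 1, apart from the negligible cost of one parameter.

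**What to change.** In section 10.1 (II. Intervention study), state the primary model as follows:

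- Outcomes: DHI at 3, 6 and 12 months.
- Fixed covariates, prespecified: baseline DHI, practice type and area.
- Terms for arm, visit and arm by visit.
- Primary estimate: the arm contrast at 12 months.

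Replace the open reference to confounders with a prespecified list of any further adjustment covariates. Align section 8.1.1 so that it describes the 12-month difference between arms given baseline DHI; at a given baseline this is the same quantity as the difference in change.

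The cost is wording only. Baseline DHI is already collected from every patient, practice type and area are needed for the randomisation itself, and the planned 250 patients need not change.

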#### 8.1.2 Secondary study parameters/endpoints (if applicable)

- Quality of life, as measured with the EQ-5D-5L.
- Dizziness frequency, defined as the number of episodes of dizziness per day, week, month and year. Dizziness frequency will be assessed using a calendar filled in by the patient during a 12 month period.
- Difference in FRID count, defined as the difference in FRID count between baseline and after 12 months follow-up.
- Presence of anxiety/depression, as measured with GAD-7, PHQ-PD, and PHQ-9.
- Fall frequency, defined as the number of falls per year. Fall incidence will be assessed using a calendar filled in by the patient during a 12 month period.
- Health care utilization. We will use the extracted data from the electronic medical records of all patients to assess the number of registered medical consultations, prescriptions, referrals, hospital admissions, and nursing home admissions.

#### 8.1.3 Other study parameters (if applicable)

Not applicable.

### 8.2 Randomisation, blinding and treatment allocation

Randomisation will take place at practice level. Randomisation will be executed by a researcher who is not involved in the selection of the practices (concealment of allocation). Practices will be randomly assigned to intervention practice or control practice. Stratification will take place for practice type (solo or group practice) and area (practice in disadvantaged areas or not) and block randomization will be used to create similar distributions in the different study arms. Randomisation of practices will be executed before inclusion of patients.

### 8.3 Study procedures

#### Questionnaires

If a patient agrees to participate in the study he/she will receive a set of questionnaires. Patients in group A (n = 125) will receive three questionnaires at baseline and at 6 and 12 months follow-up. Patients in the intervention study (group B and C, n = 250) will receive four questionnaires at baseline and at 3, 6 and 12 months follow-up. The questionnaires will be discussed later in this section.

#### Baseline assessment

All patients will be subjected to a baseline assessment of 30 minutes during a home visit or at the surgery of the patient's GP, depending on the preference of the patient and the mobility of the patient. Baseline assessment will be carried out by a physician or a trained research assistant.

The baseline assessment includes a structured interview and the TUG.

*Structured interview.* This includes record of socio-demographic characteristics, intoxications, current medication use, history of falls, dizziness characteristics, and the use of a hearing, seeing or walking aid.

*Timed 'up and go' Test (TUG)*. The TUG will be executed to assess impaired functional mobility. The TUG consists of an observation of the patient rising from a standard arm chair (approximate seat height of 46 cm), walking to a line on the floor 3 meters away, turning, returning, and sitting down again. The subject wears his regular footwear and uses his customary walking aid (none, cane or walker). No physical assistance is given. The patient starts with his/her back against the chair with his/her arms resting on the chair's arms, and his/her walking aid at hand. On the word 'go' the patient gets up and walks at a comfortable and safe pace. The patient will walk through the test once before being timed in order to become familiar with the test. A test score of  $\geq 20$  seconds reflects impaired functional mobility.

#### Structured interviews

In order to estimate the effect of attention in the intervention group, a random sample of 30 patients in the high risk usual care group (group B) will receive an additional home visit from a medical student, during which structured interviews will be conducted. This structured interview will take about 1 hour and will be about the actual impact of dizziness on the patient's everyday life.

The estimated effect of attention will be used in the final analysis of the results of the intervention study.

